### Economic evaluation

A detailed health economic analysis plan (HEAP) will be prepared by the trial health economists and approved by the Data Monitoring Committee (DMC) and Trial Steering Committee (TSC) before the trial health economist sees any data split by arm. The HEAP will be drafted before recruitment starts and will be approved before the junior health economist sees any outcome data split by arm. The senior health economist will remain fully blind until review of the first draft of the final economic analysis reports for checking when they will become fully unblinded and any future amendments to the HEAP will be made by them.

A within-trial cost-effectiveness analysis will be carried out, taking the NHS and social services perspective preferred by NICE, including relevant education-based health and social care services, given the age group. Service use will be collected in interview at baseline (covering the previous 3 months) and at the 6-, 12-, 24- and 52-week follow-up assessments (covering the period since last interview) using the Early Intervention Adult Service Use Schedule (EI-AD-SUS) [53]. The EI-AD-SUS was originally designed and successfully applied in populations of young people and young adults at risk of or with psychosis. Nationally applicable unit costs will be applied to all services (for example, NHS Reference Costs for hospital contacts, British National Formulary for medications, PSSRU Unit Costs of Health & Social Care for community-based services etc.) to estimate total costs per participant.

The primary economic evaluation will be a cost-utility analysis carried out at the 12-week follow-up, in line with the primary clinical analysis, with outcomes expressed in terms of quality adjusted life years (QALYs) calculated from the EQ-5D-Y [51], as preferred by NICE [60], and using the recommended area under the curve approach [61]. Secondary analyses will explore a) cost-effectiveness using the primary clinical measure of outcome (PANSS total score) at 12-weeks and b) cost-utility using QALYs at the 52-week follow-up. Given evidence to suggest the EQ-5D may not be particularly sensitive in psychosis populations [62], we will additionally include the Recovering Quality of Life-10items measure (ReQoL-10), a new generic self-reported outcome measure for use with people experiencing mental health difficulties, which may be more sensitive to change than the EQ-5D. The ReQoL is not appropriate as the main measure of effectiveness for the economic evaluation because it is not yet associated with preference weights to generate QALYs for use in cost-effectiveness analyses and it is currently considered suitable for people aged 16 and over. However, the inclusion of this brief measure will support exploration of the sensitivity of the EQ-5D in comparison to the ReQoL and the validity of the measure in young people under the age of 16.

Costs and QALYs will be presented as mean values by trial arm with standard deviations. Mean differences in costs and 95% confidence intervals will be obtained by non-parametric bootstrap regressions to account for the non-normal distribution commonly found in economic data [63]. Cost-effectiveness will be assessed using the net benefit approach and following standard approaches [64]. A joint distribution of incremental mean costs and effects for the two groups will be generated using bootstrapping to explore the probability that clozapine is the optimal choice compared to TAU, subject to a range of possible maximum values (ceiling ratio) that a decision-maker might be willing to pay for unit improvements in outcomes. Cost-effectiveness acceptability curves will be presented by plotting these probabilities for a range of possible values of the ceiling ratio [65]. These curves are the recommended decision-making approach to dealing with the uncertainty that exists around the estimates of expected costs and expected effects associated with the interventions under investigation and uncertainty regarding the maximum cost-effectiveness ratio that a decision-maker would consider acceptable. To provide more relevant treatment-effect estimates, all economic analyses will include adjustment for the variable(s) of interest and baseline covariates [66], which will be prespecified and in line with the clinical analyses. Complete case analyses will be carried out with the impact of missing data explored in sensitivity analyses. The pattern of missing data and the plausibility of assuming the data are Missing at Random will be examined for missing cost and EQ-5D-Y tariff values. Any variables predictive of missingness or predictive of response (at *P* < 0.1) will be included in the equation to impute missing values.

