### Aim and objectives

The purpose of the trial is to assess whether clozapine is more effective than TAU (standard antipsychotics) in young people with TRS in real-world settings, over a 12-week period, at the level of clinical symptoms, patient-rated outcomes, quality of life and cost-effectiveness. The primary objective is to compare the treatments on the change in total Positive and Negative Syndrome Scale (PANSS) [44] score from baseline to 12 weeks. The secondary objectives are to compare the treatments on function, adverse effects, quality of life, subjective improvement, and cost-effectiveness.

In the CLEAR trial the following hypotheses will be tested:Primary hypothesis: clozapine will be more effective than TAU after 12 weeks of treatment as demonstrated by reduction in PANSS total scoresSecondary hypotheses:Clozapine will lead to a higher global improvement than TAU as measured by the CGI at 12 weeks, 24 weeks, and 52 weeksClozapine will lead to a better improvement in health-related quality of life than TAU as measured by EQ-5D-Y at 12 weeks, 24 weeks, and 52 weeksClozapine will be cost-effective compared to TAU at 12 weeks, 24 weeks, and 52 weeksThe prevalence of adverse effects in participants on the clozapine arm will be higher than TAU at 12 weeks as measured by the GASS-C, weight, and metabolic laboratory measurements (i.e., higher HbA1C and lipids)The clozapine arm will be more likely to remain on the same medication longer-term than TAU, as measured by medication use at 24 weeks and 52 weeks.Mechanistic hypotheses:Improvement in schizophrenia symptom severity during clozapine treatment compared to TAU will be mediated by anti-inflammatory and glutamatergic mechanisms. The biomarkers characterising these anti-inflammatory and glutamatergic mechanisms will include reductions in peripheral proinflammatory cytokines (e.g., IL-6), brain glutamate and rCBF, and increases in anti-inflammatory cytokines (e.g., IL-10) and peripheral and central oxidative defence (GSH) from baseline to 12 weeks.

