### Sample size

The standardised mean difference for clozapine versus other antipsychotics in adults based on PANSS total score at 12 weeks is 0.39 [55]. The standard deviation of the PANSS score at 12 weeks in our similar sample of treatment resistant patients being started on clozapine [43] is 14.2 (60% CI 12.96–16.20). Using an upper limit of the 60% confidence interval [56], an effect size of 0.39 corresponds to a between group difference of 6.4 points. In our previous research [43], the 95% CI for the baseline-12-week correlation in the sample was 0.553 to 0.880, and we use a value of 0.5. This is conservative but realistic, since the time points are only 12 weeks apart. Under these assumptions, and assuming 20% attrition to 12-week follow-up, the target sample size to recruit at baseline is 260 participants.

For the mechanistic study we estimate that, of all participants recruited at MRI sites, 50% will agree to participate in MRI. This results in a sample for the mechanistic study of 90 participants at baseline and, assuming 20% attrition, complete mechanistic data in 70 participants. This sample size has 80% power to detect a minimum between group effect size of 0.7SD on a standardised scale and 90% power for 0.8SD. In our previous observational study in TRS [43], we found a within-group effect after 12 weeks of clozapine of 0.7. Assuming there is no further change from prior treatment in the standard antipsychotic treatment arm on these measures over 12 weeks, we would have sufficient power to detect between-group effects of these magnitudes and expect the effect sizes to be greater in the younger population.

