### Statistical analysis

The Statistical Analysis Plan will be drafted within 6 months after recruitment starts and will be approved by the Data Monitoring Committee (DMC) and Trial Steering Committee (TSC) before the junior statistician sees any outcome data split by arm. The senior statistician will remain fully blind throughout the study.

We will report data in line with the CONSORT 2010 statement [57] showing attrition rates and loss to follow-up. The target estimand is the treatment policy estimand, and all primary and secondary analyses will be carried out following the intention to treat principle, incorporating data from all participants including those who do not complete treatment. Every effort will be made to follow up all participants in both arms for research assessments. The trial will be blind rated to minimize observer bias. The primary analysis will be conducted after the final 12-week follow-up assessment is completed for the final patient recruited into the study. The study team including CI and trial statisticians will be aware of the results of the primary analysis from this point. The remaining 24-and 52-week assessments will continue to be conducted blind to individual patient’s allocation. We will analyse the 24- and 52-week outcomes in a secondary analysis.

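### The base case of the economic evaluation is complete case, with imputation only as a sensitivity analysis; this does not match the available-data approach of the clinical analysis and can bias incremental costs and QALYs

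*Protocol article*

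**What the plan says.** All references are to the protocol article.

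- **Economic evaluation, main analysis:** "The primary economic evaluation will be a cost-utility analysis carried out at the 12-week follow-up, in line with the primary clinical analysis". QALYs come from the EQ-5D-Y by area under the curve. A cost-utility analysis at 52 weeks is secondary.
- **Economic evaluation, missing data:** "Complete case analyses will be carried out with the impact of missing data explored in sensitivity analyses". The section then plans to examine the pattern of missing data and the plausibility of MAR, and to impute using variables that predict missingness or response at P < 0.1. All economic analyses adjust for prespecified baseline covariates.
- **Statistical analysis, general rule:** "all primary and secondary analyses will be carried out following the intention to treat principle, incorporating data from all participants". The same sentence names treatment policy as the estimand and, on who is kept, adds: "including those who do not complete treatment".
- **Statistical analysis, model:** clinical outcomes are analysed by linear mixed models fitted to all outcomes up to week 12, which the section describes as valid under MAR given the covariates.
- **Aim and objectives:** "The secondary objectives are to compare the treatments on function, adverse effects, quality of life, subjective improvement, and cost-effectiveness".
- **Sample size:** "assuming 20% attrition to 12-week follow-up, the target sample size to recruit at baseline is 260 participants".

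**The concern.** The main clinical and main economic results share the same 12-week horizon but treat incomplete follow-up differently. The clinical model keeps a participant who was seen at week 6 and lost by week 12. The economic base case drops that participant, although the 6-week service-use interview and PANSS are informative about the missing cost and utility.

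A complete-case comparison needs missingness to be unrelated to costs and QALYs once arm and the adjusted baseline covariates are allowed for, or related in the same way and at the same rate in both arms. The plan itself gives reasons to doubt this. Treatment is open label. The hypotheses expect more adverse effects on clozapine and longer persistence with it. The Statistical analysis section also provides for adherence being associated with missing clinical data.

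At 52 weeks there is a further loss. Participants who cannot be reached are followed through case notes, which may yield service use but are unlikely to yield an EQ-5D-Y response. Complete case would then discard observed costs from the people who are hardest to reach.

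At stake are the incremental cost, the incremental QALY and the acceptability curve, and so the headline cost-effectiveness conclusion.

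**Working it through.** **1. Reproduce the planned sample size, to fix what 20% attrition leaves.** Inputs from the Sample size section: standardised difference 0.39, baseline to 12-week correlation 0.5, attrition 20%, target 260. The article gives no alpha or power for the primary outcome; two-sided 0.05 and 90% are assumed here.

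n per arm = 2 × (1.960 + 1.282)² × (1 − 0.5²) / 0.39² = 2 × 10.51 × 0.75 / 0.1521, which is just under 104.

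Total 2 × 104 = 208, and 208 / 0.80 = 260. The stated figure reproduces. (80% power with no baseline adjustment also gives 104 per arm and 260, but ignores the stated correlation.)

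**2. Ceiling on complete cases at 12 weeks.** 260 × 0.80 = 208, so at least 260 − 208 = 52 randomised participants are left out. More are lost if anyone who stays lacks a needed EQ-5D-Y or service-use record. The document gives no rate for that, so this further loss is not sized.

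**3. What is discarded.** Service use is collected at baseline and at 6, 12, 24 and 52 weeks (Economic evaluation). PANSS is analysed at 6 and 12 weeks (Statistical analysis). For someone lost between weeks 6 and 12, both 6-week records may exist. The mixed model uses the PANSS; the complete-case economic analysis uses neither.

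**4. Can this bias the comparison?** The document gives no SD for EQ-5D-Y or cost, so the check is a large simulation on a standardised outcome. Assumed inputs: true difference 0; correlation 0.5 between baseline and week 6, and 0.7 between week 6 and week 12; where dropout depends on 6-week status, a log-odds slope of 1 per SD. Two estimates are compared: a baseline-adjusted complete-case regression, and a MAR analysis by arm that uses the 6-week value.

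| Dropout mechanism | Attrition by arm | Complete-case bias (SD) | MAR bias (SD) |
|---|---|---|---|
| Unrelated to status | 20% / 20% | 0.00 | 0.00 |
| Related equally in both arms | 20% / 20% | 0.00 | 0.00 |
| Related equally, rates differ | 15% / 25% | −0.04 | 0.00 |
| Related in one arm only | 20% / 20% | −0.09 | 0.00 |
| Related in opposite directions | 20% / 20% | −0.19 | 0.00 |

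The signs follow from how the scenarios were set up and predict no direction for this trial. MAR holds by construction in every row, so the last column shows what the 6-week data can recover when MAR is true, not that MAR will be true.

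**The case against.** The strongest reply is that little is missing from the plan. The Economic evaluation section already commits to examining MAR and to imputation, all economic analyses adjust for baseline covariates, and details belong in the HEAP, which is not shown. Both analyses will be reported under either ordering. That stands as far as it goes. The ordering is nevertheless a stated choice rather than a detail left open, and the base case is what carries the headline result.

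A reader might also infer four stronger points, which the document does not support.

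- **That complete case contradicts the intention-to-treat rule.** The rule sits in the clinical statistics section and names people who stop treatment. A complete-case analysis by randomised arm keeps them when their data are complete. Cost-effectiveness is a secondary objective, so a literal reading does reach the economic analyses, but the result is a mismatch to reconcile. The phrase about being in line with the clinical analysis may refer only to the 12-week timing.
- **That stopping treatment removes a participant.** The section on data collection says that follow-up will still be sought, with permission, after withdrawal from study drug alone.
- **That one missed form always removes a participant.** Each service-use interview reaches back to the previous one, so a missed 6-week interview may be covered at week 12. The readable text does not state a 6-week EQ-5D-Y, and the schedule figure is not shown. Multiplying assumed missing rates across forms would overstate the loss, since the same research assistants collect both instruments and missed visits would tend to remove both together.
- **That the two analyses rest on wholly different populations.** Participants with no post-baseline outcome contribute essentially nothing to the mixed model either.

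**Conclusion.** The point holds as a weak choice of base case and a mismatch with the clinical analysis. The firm figure is that at most 208 of 260 participants (80%) enter the primary cost-utility analysis at the planned attrition, so at least 52 are left out, with any interim data they gave.

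Bias is possible, not certain. In the assumed scenarios it was nil when dropout was unrelated to status, or related identically and at equal rates in both arms. It reached about 0.19 SD when the relation ran in opposite directions. These values rest on the assumed correlations, slope and zero true difference. Neither size nor direction in QALYs or pounds can be derived from the document.

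**What to change.** In the HEAP, make the imputation that is already planned the base case at both 12 and 52 weeks: multiple imputation by arm, using baseline covariates and the observed interim cost, utility, PANSS and adherence data, combined with the bootstrap. Report complete case as the sensitivity analysis.

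State also whether the all-participants rule in the Statistical analysis section covers the economic analyses. If complete case is kept as the base case, say that the rule does not apply there and justify the choice. Settle this before anyone sees data by arm, because choosing between discordant results afterwards would be open to criticism.

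The cost is mainly wording, since the selection of imputation predictors is already specified. There is slightly more computing from combining imputation with the bootstrap, and the headline result then relies on the imputation model and on MAR. No change to data collection or sample size is needed.

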### Safety

Participants will be asked at each visit from consent onwards to report any suspected adverse reactions. Any suspected adverse events will be recorded from consent visit to end of trial. Any suspected adverse events recorded will be explored again at each visit thereafter. Events or reactions listed in the Summary of Product Characteristics (SmPC) do not need to be reported unless they fulfil seriousness criteria.

All Serious adverse Event (SAE), Serious Adverse Reaction (SAR) or Suspected Unexpected Serious Adverse Reaction (SUSAR), excepting those specified in the protocol as not requiring reporting, will be reported immediately by the CI (and certainly no later than 24 h) to the KHP-CTO in accordance with the current Pharmacovigilance Policy. The KHP-CTO will report SUSARs to the regulatory authority (MHRA).

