### Outcomes

The primary outcome is the change in total blind rated PANSS total scores at 12 weeks from baseline.

Secondary outcomes include: blind rated change in overall Clinical Global Impression Scale (CGI) [48], clinician rated level of adherence (CRS) [49], adverse effects (GASS-C) [50], health-related quality of life (EQ-5D-Y) [51], subjective experience (DAI-10) [52], readmission rate, (EI-AD-SUS) [53], and change in PANSS sub-scale (positive, negative and general) [44]. We will also combine these outcomes (EQ-5D-Y and total PANSS score) with service use data (EI-AD-SUS) to compare treatments on cost-effectiveness.

Patients will be followed up for 12 months with the potential for further follow-up using clinical records for longer-term evaluations.

For the mechanistic study, outcomes include the change in brain glutamate, regional cerebral blood flow (rCBF) and GSH, and peripheral cytokines and GSH from baseline to 12 weeks.

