### Assessments

#### Clinical trial

Centralised, remote, blind assessments by Research Psychiatrists will include:PANSS, the primary outcome. It is the most well validated standardised rating scale in clinical trials of psychosisCGI. It is simple and designed to capture the overall clinical judgement of an experienced clinician. CGI-Severity (CGI-S) will be assessed at baseline, and CGI-Improvement (CGI-I) will be assessed in the following visits.

Data collected by Research Assistants (RAs) will include:Medical history: Full history of antipsychotic use, doses, and responsePatient-rated outcome measure (PROM): Drug Attitude Inventory (DAI-10)Adverse events: Glasgow Antipsychotic Side-effect Scale for Clozapine (GASS-C). It is a modification of the GASS, a well validated side effect scale, with additional questions pertaining to common adverse effects of clozapineAdverse events: spontaneous report. The RAs will prompt for any other suspected adverse reactions and record theseAdherence: Clinician Rating Scale (CRS)Health-related quality of Life: EQ-5D-Y, a questionnaire which is used to generate quality adjusted life years (QALYs) for use in economic evaluation, as recommended by NICEService use for economic evaluation: Early Intervention Adult Service Use Schedule (EI-AD-SUS), a measure specifically designed for use in children and young adults with psychosisRecovering Quality of Life-10 items measure (ReQoL-10) [54], a measure of health-related quality of life specifically designed for users of mental health services.

Laboratory measurements will be collected at baseline and at 12 weeks. Blood tests include HbA1c, lipids, prolactin, and liver function tests. As per standard care, the clozapine arm will undergo weekly blood monitoring to check full blood count and clozapine plasma levels as per standard care.

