### Blinding

The raters for primary outcome (PANSS) and CGI-S and CGI-I will be centralised and blinded to minimise observer bias. The participants, the treating team, and the rest of the trial team will not be blinded. There will be four blinded members of the study team: two research psychiatrists, one for adult participants and the other for child participants (each with appropriate training for that age group), the Chief Investigator (CI) and Co-Chief Investigator. They will not be informed which treatment arm the participants are in and will not enquire about the participant’s treatment or side effects.

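### Spontaneous events are elicited as suspected adverse reactions, by unblinded staff from unblinded participants, so these counts are open to attribution that depends on the arm

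*Protocol article*

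**What the plan says.** Spontaneous reports are described in three places in the protocol article, in differing terms.

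- **Safety:** "Participants will be asked at each visit from consent onwards to report any suspected adverse reactions". The next sentence changes the term: "Any suspected adverse events will be recorded from consent visit to end of trial".
- **Assessments, Clinical trial:** the entry is labelled as spontaneous report of adverse events, but the action is "The RAs will prompt for any other suspected adverse reactions". The word *other* places this prompt after the GASS-C, the structured side-effect scale.
- **Follow-up period:** at 24 and 52 weeks the item is spontaneous adverse events, with no mention of suspicion.

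On who knows the allocation, the Blinding section says "The participants, the treating team, and the rest of the trial team will not be blinded". Four roles stay blinded: two research psychiatrists and the two chief investigators. Research assistants are not among them.

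On the planned comparison of harms, the hypothesis under Aim and objectives is that adverse effects on clozapine will be "higher than TAU at 12 weeks as measured by the GASS-C, weight, and metabolic laboratory measurements". The harm measure listed under Outcomes is the GASS-C. For blood tests, "Laboratory measurements will be collected at baseline and at 12 weeks".

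**The concern.** An adverse event is any untoward occurrence. An adverse reaction is one thought to be caused by a drug. The article's own abbreviation list keeps the two apart. Asking for suspected reactions makes the participant or the research assistant judge cause before anything is written down, and both know the arm when they do so.

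Two things are at stake. First, if willingness to blame the drug differs between arms, the recorded counts differ even when the true risks do not. Second, an event that nobody yet links to treatment may not be mentioned at all, in either arm. That matters in a trial whose Discussion in the abstract promises knowledge on safety, and whose Data monitoring section has a committee reviewing accruing safety information. The sentence on recording suspected adverse events does not repair this, because recording cannot recover an event that was never asked about.

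**Working it through.** The plan gives no figure on this point, so there is none to reproduce. The check has two parts.

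**1. Which harm data pass through the prompt**

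| Source | Section | Needs prior attribution? |
|---|---|---|
| GASS-C | Aim and objectives; Outcomes; Assessments | Not as described |
| Weight | Aim and objectives | No |
| Metabolic laboratory tests | Aim and objectives; Assessments | No |
| Serious adverse events | Safety | Not as described: reportable as events, listed separately from serious reactions, subject to protocol exceptions |
| Non-serious spontaneous reports, 12-week trial | Safety; Assessments | Yes, by the stated prompt |
| Spontaneous reports, 24 and 52 weeks | Follow-up period | Not by the wording there |

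The filter therefore acts on the non-serious spontaneous reports collected during the 12-week trial.

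**2. What the filter could do to that row (illustration on assumed figures)**

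Let p be the true proportion with an event, equal in both arms. Let a_C and a_T be the proportions of those events attributed, and so recorded, on clozapine and on TAU. Then:

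- recorded proportions: p × a_C and p × a_T
- recorded risk ratio: (p × a_C)/(p × a_T) = a_C/a_T, whatever p is

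From Sample size: 260 randomised 1:1 is 130 per arm, and 20% attrition leaves 130 × 0.8 = 104 per arm. The values of p, a_C and a_T are assumptions. The chance of a nominally significant difference (two-sided 0.05) uses the normal approximation for two proportions, Φ[(|p₁ − p₂| − 1.96 × SE₀)/SE₁], with SE₀ pooled and SE₁ unpooled.

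With p = 0.40:

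| a_C | a_T | Recorded | Risk ratio | Chance of spurious significance |
|---|---|---|---|---|
| 0.80 | 0.80 | 0.32 v 0.32 | 1.00 | 5% |
| 0.90 | 0.80 | 0.36 v 0.32 | 1.13 | 9% |
| 0.90 | 0.70 | 0.36 v 0.28 | 1.29 | 23% |
| 0.90 | 0.50 | 0.36 v 0.20 | 1.80 | 73% |

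Worked line for 0.90 v 0.70: SE₀ = √(2 × 0.32 × 0.68/104) = 0.0647; SE₁ = √((0.36 × 0.64 + 0.28 × 0.72)/104) = 0.0645; (0.08 − 1.96 × 0.0647)/0.0645 = −0.73; Φ(−0.73) = 0.23.

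Over true risks of 20% to 60%, the last column for the three unequal rows runs from 6% to 95%.

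The direction is also open. If attribution were 80% on clozapine and 90% on TAU, the ratio would be 0.80/0.90 = 0.89, and the filter would hide harm.

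The loss of events needs no difference between arms. At 80% attribution in both, the ratio is unbiased, but 0.40 − 0.32 = 0.08 of participants have an event that goes unrecorded.

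**The case against.** The case against has several parts.

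- **The stated harm comparison is elsewhere.** It rests on the GASS-C, weight and laboratory values, and the article plans no between-arm test of spontaneous counts. This stands, and it limits the point to the spontaneous channel. The GASS-C is also collected unblinded, but that is ordinary open-label reporting bias and a different mechanism.
- **Other channels exist.** Serious events are reportable as events, and service use and readmission are collected. This stands too: a reader might infer that an unsuspected event can never surface, but for serious events that does not follow.
- **The direction is not given.** One might suppose that clozapine is new to the participant and the comparator familiar. Under Interventions, however, TAU is an oral non-clozapine antipsychotic agreed with the participant and titrated, so people in that arm may also be starting a new drug.
- **This is a condensed article.** The full protocol, the visit script and the case report form are not shown, and the shift between terms may be loose summary wording. That is possible. Yet the narrow prompt appears in both sections that describe elicitation during the trial, so it is a stated rule and not an omission.
- **A neutral question does not blind anyone.** True: arm-dependent reporting would remain. What goes is the explicit causal screen placed before recording.

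The Safety section also says "Events or reactions listed in the Summary of Product Characteristics (SmPC) do not need to be reported unless they fulfil seriousness criteria". That rule on reporting is a separate matter and is not relied on here.

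**Conclusion.** The point holds for spontaneously reported, non-serious events during the 12-week trial. Followed as written, the prompt puts an arm-aware judgement of cause before recording, and the article uses three terms for the same data without reconciling them. Such counts are open to differential attribution, and unsuspected non-serious events may be lost.

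A reader might go further and conclude that the trial's between-arm harm comparison is biased. The document does not support that: the pre-specified GASS-C, weight and laboratory comparisons do not depend on this prompt.

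The bias is a risk and has not been shown to occur. Its size depends wholly on a_C/a_T, which the document does not give. The illustrative ratios of 1.13 to 1.80 assume equal true risk, one yes/no event per participant and attribution higher on clozapine. Equal attribution gives 1.0, and the reverse pattern gives a ratio below 1. The change is worth making because it is cheap, the trial is described as in set-up, and events never recorded cannot be reliably recovered later.

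**What to change.** 1. In both arms and at every visit, ask one neutral open question about any new or worsened medical problem since the last visit.
2. Record each such event whatever its suspected cause, and assess relatedness afterwards in a separate field.
3. Use the same term in Safety, in Assessments (Clinical trial) and in Follow-up period, and bring the visit prompt and case report form into line.
4. Base any between-arm summary of spontaneous events on all recorded events, not on those judged related, and state that open-label reporting bias remains.

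The cost is a change of wording in the protocol, prompt and case report form, and somewhat more non-serious events to enter. The sample size, visit schedule and planned GASS-C, weight and laboratory comparisons are unaffected.
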